#### Quantitative data.

We will compare the distribution of patient characteristics between the unexposed observations from the control period and the exposed observations during the intervention period overall and within each center to identify potential confounders. Then, we will plot rates of initial (primary clinical outcome) and refilled PrEP prescriptions (secondary clinical outcome) over each time period, comparing how rates differ from the control period to the intervention period across all centers and within each center, to examine the effects of the intervention site and time on the outcomes. To examine the treatment effect, a generalized linear mixed-effects model will be used, with a random intercept for each PPIL site and fixed effects for the intervention and for each time interval [27], where the fixed effect for each time interval is included to account for secular trends. Any identified potential confounders will also be included as fixed effects in the model. An intention-to-treat analysis will be used to ensure a conservative estimate of the intervention effect in the case that a site deviates from the assigned intervention timeline or has low intervention fidelity. Additionally, any identified potential mediators will be investigated. We will carefully monitor the timing and measure of the impact of the availability of new PrEP modalities (i.e., long acting injectables) on intervention effects. Their potential influence on intervention effects will be addressed by including indicator variables for the time periods in which these PrEP modalities become available. We will adopt complete case analysis to deal with missing covariates in the primary analysis. To assess the robustness of our findings, we will perform sensitivity analyses using multiple imputation models that account for clustering by site, study period, and intervention status [28]. Additional exploratory sensitivity analyses will include missing-indicator approaches for covariates, acknowledging their limitations and the potential for bias. We anticipate all results to be available by December 2029.

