### Guiding theories and frameworks

The Social Ecological Theory is the guiding theory that underlies EUPHORIA. This theory highlights that an individual’s behavior and health-related decisions are embedded in an intersectional context (provider, health center, etc.) [12]. Research has consistently shown that barriers within healthcare are driven and sustained by multi-level factors and interventions that fail to consider such overlapped levels will likely fall short of achieving a comprehensive understanding of the drivers of health disparities [13–15]. The Social Ecological Theory can be leveraged to identify high-impact points within health centers and center task flow that can facilitate the successful implementation of interventions. Our proposed implementation strategies to support PrEP uptake among women address multiple levels including the individual (patient education), provider (provider training), health center system (EHR tools), and broader health system (PrEP navigation, clinical champion) (Table 1).

**Table 1 pone.0355623.t001:** EUPHORIA intervention package of strategies.

Strategy	Description
Routine PrEP education	PrEP education provided at each clinic visit to all Black women
Standardized provider training	3 sessions of 2-hour virtual trainings covering identifying PrEP-eligible women, working with the PrEP navigator/navigation team, and practicing difficult conversations with virtual Black women patients (avatars)
EHR tools	Incorporate the PrEP indication documentation into the EHR; provide monthly reports of PrEP continuum outcomes for clinic staff
PrEP navigation, clinical champion	Trained PrEP navigator to meet with patients to support PrEP uptake, monthly check-in with patients thereafter to support retention and adherence; follow-up appointments offered in-person or via telehealth; PrEP expert who can guide clinicians in implementing the EUPHORIA strategies

PrEP: Pre-exposure Prophylaxis; EHR: Electronic Health Record

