#### Implementation and post-implementation phases.

All outcome data to be collected are part of existing routine EHR data collection at PPIL. PPIL Information Technology (IT) will create custom reports in the PPIL data warehouse to be built utilizing the existing data fields and a table of desired variables (Table 3).

**Table 3 pone.0355623.t003:** Requested electronic health record variables within limited data set.

Data domain	Brief description
Denominator/overall PrEP eligibility	Number of patients who are eligible to learn more about and receive PrEP according to study criteria: all patients 12 years or older, who are not living with HIV, and who have had a relevant medical encounter (e.g., family planning, sexual health care, primary care, etc.) during which PrEP could be prescribed *PrEP ineligibility: Patient is less than 12 years old or is medically unable to use PrEP (e.g., living with HIV) or attends a medical encounter during which PrEP is unlikely to be discussed or prescribed.
PrEP eligibility characteristics	STI screening history, risk factors, prior PrEP visits, and HPI for PrEP, visit date, visit type, location of care
Primary and secondary outcome measures	
PrEP initiation (i.e., initial prescription) – primary outcome	Proportion of Black women at each site who receive an initial prescription for PrEP (i.e., have not received a prescription for PrEP in the prior six months)
PrEP persistence (i.e., subsequent/refill prescription) – secondary outcome	Proportion of Black women at each site who receive a subsequent prescription of PrEP after initiating PrEP (i.e., refill initial prescription within six months)
Process measures	
HIV risk assessment	Proportion of eligible Black women who undergo HIV risk assessment at each site
PrEP education	Proportion of eligible Black women who receive PrEP education at each site
PrEP navigation	Proportion of eligible Black women who are referred to PrEP navigator at each site
Sociodemographic data/covariates	Gender identity, sex assigned at birth, sexual orientation, race, ethnicity, date of birth, gravidity, parity, annual income, preferred language, home zip code, marital status, disability status, HIV status, STI testing and diagnosis history within past year, location of care, prescription name(s) and duration(s)

PrEP: Pre-exposure Prophylaxis; STI: Sexually Transmitted Infection; HPI: History of Present Illness

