Reports will be built to monitor (1) EHR alert consistency, (2) if PrEP is offered, (3) if PrEP is accepted or declined, and (4) among those who accept, if patient navigation is utilized and if PrEP is prescribed. These data will be collected at the health center level and during two phases: 1) the control, or baseline phase and 2) the intervention phase. The control and intervention phases are of variable length depending on step assignment (Fig 1). Implementation outcomes of each health center will be assessed at the midpoint and endpoint of the intervention period.

The initiation of PrEP prescriptions for eligible Black women (primary clinical outcome) will be measured using de-identified patient-level EHR data. Eligibility for inclusion in the outcome measures among patients will be determined based on study inclusion criteria such as patient’s age, biological sex and gender identity, and race. The primary outcome will be the proportion of eligible Black women at each health center who receive a prescription for PrEP during that month. The secondary outcome will be PrEP refills within six months, i.e., receipt of a PrEP prescription within six months of the index visit among those in the eligible population with a prior PrEP prescription. Finally, the total number of PrEP prescriptions among all patients in the control (baseline) and intervention periods will be analyzed to determine the impact of the implementation strategies on the entire PPIL patient population.

At approximately the midpoint of each site’s intervention period, key informant interviews including focus groups and interviews will be conducted with PPIL staff, clinicians, and women to assess implementation outcomes such as acceptability, feasibility, and fidelity over time. These interviews will elicit information related to the barriers and outcomes encountered during implementation. Procedures for recruitment and enrollment for these participants will mirror those of pre-implementation qualitative data collection completed as part of Aim 1. Data will be coded according to the RE-AIM constructs, with emerging themes identified and categorized by implementation outcome: acceptability, feasibility, and fidelity (Table 4). The usage of mixed methods in this study will be used to elaborate on quantitative RE-AIM findings with themes from qualitative data. Participant recruitment and data collection are expected to be completed by June and December 2028, respectively.

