#### Sample size.

This study will be powered to determine whether there is a statistically significant difference in PrEP prescriptions among at-risk Black women defined as those with a positive STI test accessing family planning services between the intervention and control periods. We choose to use presenting to a family planning clinic and a positive STI test (gonorrhea, chlamydia, or syphilis) as eligibility to ensure patients at high risk for HIV acquisition are offered PrEP within the PPIL context, keeping in line with the CDC’s guidance to offer PrEP to patients at substantial risk of HIV acquisition. A power calculation was conducted based on a mixed effects effectiveness model with a random intercept for clinic and intervention and time as fixed effects. Assuming a baseline PrEP uptake of 1% and a conservative intraclass correlation coefficient (ICC) of 25%, a trial with 10 PrEP-eligible Black women per month (30 women per step) at each of the 8 clinics (8 steps) would allow us to detect an increase to 5% PrEP uptake (corresponding to an odds ratio of 5.21 for the intervention effect) in eligible Black women following the introduction of the intervention with >90% power at a two-sided alpha of 0.05. Our sample size provides almost 100% power for detecting a larger increase to 15% PrEP uptake (corresponding to an odds ratio of 17.47 for the intervention effect). Our sample size accounts for both the clustered nature of the design and the potential confounding effect of time. We used R software for power analysis.

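### Two conflicting rules for the primary outcome (any prescription in the month, or initial prescription only) give very different false-positive rates under the planned site-intercept model

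*Protocol article*

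**What the plan says.** **Primary outcome, monthly sentence.** The Implementation and post-implementation phases section, working from patient-level EHR data, states: "The primary outcome will be the proportion of eligible Black women at each health center who receive a prescription for PrEP during that month". It does not say that the prescription must be a first one.

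**Primary outcome, everywhere else.** Table 3 in the same section calls the primary outcome initiation. It counts a woman only if she "have not received a prescription for PrEP in the prior six months". Study design speaks of prescriptions initiated, and the paragraph holding the monthly sentence itself opens with initiation. Quantitative data plans to "plot rates of initial (primary clinical outcome) and refilled PrEP prescriptions (secondary clinical outcome".

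**Secondary outcome.** The same paragraph defines it as "receipt of a PrEP prescription within six months of the index visit among those in the eligible population with a prior PrEP prescription". Table 3 ties it to a refill of the initial prescription within six months, and Study design to those who initiate.

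**Model.** Quantitative data states that "a generalized linear mixed-effects model will be used, with a random intercept for each PPIL site and fixed effects for the intervention", plus a fixed effect for each time interval. The only random effect is the site. The multiple-imputation sensitivity analyses list site, study period and intervention status as what they account for, again without the patient.

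**The concern.** A site random intercept with period effects treats records as independent once site and period are known. If any prescription in a month counts, a woman prescribed in three different months gives three positive records that the model takes as three separate successes. Prescribing is expected to be near 1% at baseline, so a few continuing users could supply many of the positives, and their chance clustering in one condition could look like an effect. The strategies might then be declared effective, and scale-up supported, when nothing had changed.

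Under the initiation rule a woman cannot score again within six months of a prescription, and this mechanism largely disappears. The article contains both rules, so the error rate of the main test depends on which one the analyst codes.

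**Working it through.** **Plan's own figures first.** The Sample size section gives 1% to 5% as an odds ratio of 5.21, and 1% to 15% as 17.47:

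- (0.05/0.95)/(0.01/0.99) = 5.21
- (0.15/0.85)/(0.01/0.99) = 17.47

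Both agree. Power was simulated with the stated logistic mixed model at 8 sites, 30 women per site per step and ICC 0.25. On the latent logit scale the site variance is (0.25/0.75) × π²/3 = 1.097. With every woman independent, power at OR 5.21 is 94% with no transition gap, and 88–90% with transition data dropped. At OR 17.47 it is 100%. The stated power of more than 90% is therefore reproduced for independent women when transition data are not dropped.

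**Type I error.** The same type of model (site intercept, quarter fixed effects, intervention) was fitted to data with no intervention effect and tested by likelihood ratio against 3.84. Two separate set-ups were used, both with about 1% of woman-months carrying a prescription:

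- *Set-up A:* sites sized from Table 2; constant site effects with SD 0.5; 2 eligible visits per woman per year (4 also tried); a geometric number of prescriptions per user with mean 1, 2 or 3, at gaps of 1 or 3 months; a 30-month layout with transition quarters dropped and a 27-month layout without them; 400 runs per cell (Monte Carlo SE about 1–2 points).
- *Set-up B:* 10 women per site per month, or Table 2 volumes divided by 12; site variance 1.097; mean time on PrEP 3, 6 or 12 months with monthly supply, and 6 or 12 months with three-month supply; 9 or 10 periods with transition data dropped; 1,000 runs per cell (SE about 0.7 points near 6%, 1.4 near 30%).

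Visit frequency, prescriptions per user, time on PrEP and supply length are assumptions. The article lists prescription duration as a variable to collect but gives no value.

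| What counts as a success | Set-up A | Set-up B |
|---|---|---|
| Reference: one prescription per user (A); independent woman-months (B) | 6–9% | 5.6–7.0% |
| Initial prescription only | 5–9% | 5.1–7.4% |
| Any prescription, three-month supply | 9–10% | 8–12% |
| Any prescription, monthly supply | 16–29% | 24–34% |

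Within the last row, set-up A gives 16–21% with a mean of 2 prescriptions per user and 23–27% with 3 (25–29% at 4 visits per year).

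**What causes the excess.** In set-up B, continuing users stay in the denominator under the initiation rule, yet the rejection rate matches that for independent records. Repeat entry therefore adds no visible inflation; repeated successes do. The small excess over 5% also appears in the reference row, so it does not come from repeat records.

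**What removes it.** In set-up A, site and period fixed effects with the variance clustered on the woman reject 4–9% of the time in all these cases. For a mean of 3 monthly prescriptions:

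| Layout | Planned mixed model | Fixed effects, naive variance | Fixed effects, woman-clustered | Initial only, mixed model |
|---|---|---|---|---|
| 30-month | 27.0% | 28.5% | 6.2% | 5.2% |
| 27-month | 22.5% | 22.8% | 8.5% | 5.5% |

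**Secondary outcome.** No rejection rate was computed. The issue is textual. The paragraph's wording lets each visit by a woman with a prior prescription serve as an index visit, with overlapping six-month windows. Table 3 allows only the refill that follows the initial prescription.

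**The case against.** The strongest reply is that the primary outcome is initiation. Table 3, Study design, Quantitative data and the opening of the very paragraph in question all say so, which makes the monthly sentence plausibly shorthand. Under initiation the planned model behaves properly. This stands, and it rules out two stronger readings.

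A reader might infer that the model is invalid simply because the same woman appears in several months. The initiation results show otherwise.

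A reader might also take 16–34% as the trial's expected false-positive rate. That needs both the literal monthly sentence and monthly supplies, and the article does not give a supply length. Table 1 does offer "monthly check-in with patients thereafter to support retention and adherence; follow-up appointments offered in-person or via telehealth", but this is navigator contact and follow-up within the intervention package. It does not establish monthly prescribing, least of all under control.

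Nor does the Sample size section show an error on this point. Its figure of "10 PrEP-eligible Black women per month (30 women per step") is a planning count, and nothing there says that the 30 include repeats. Repeats are plausible at the two centers with 144 Black women in 2023, since 10 × 12 = 120 distinct women would be 83% of them (120/144). That is not proof.

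Finally, an article may leave record structure and variance estimation to an analysis plan. That excuses brevity but not two different outcome rules in one document.

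**Conclusion.** The conflict is real and should be resolved before outcome data are extracted. Under the initiation rule the planned test is close to nominal, at about 5–9%. Under the literal monthly wording it rejects about 8–12% of the time with three-month supplies and about 16–34% with monthly supplies. These ranges rest on 1% prescribing, no true effect, and the assumed visit frequency, time on PrEP, prescriptions per user and supply length. The direction is firm; the size under the monthly wording is conditional on those assumptions. A re-initiation more than six months after the last prescription could still be a second success for one woman, and this was not modelled separately. For the refill outcome, only the conflict of wording is established.

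**What to change.** 1. In the Implementation and post-implementation phases section, reword the monthly sentence so that the primary outcome is an initial prescription with the six-month look-back of Table 3.
2. Define the refill outcome from one index (initial) prescription per woman, as Table 3 implies.
3. If any analysis keeps repeated prescriptions or index visits per woman, state in Quantitative data that the variance accounts for the woman. One option is site and period fixed effects with variance clustered on the de-identified patient ID, which is the version checked here. It replaces the site random intercept in that analysis. A woman-level random intercept nested in site is an alternative, but it was not tested.

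The cost is wording and, where repeats are kept, one variance option with somewhat wider confidence intervals. The patient key it needs is already required by the six-month look-back and the refill outcome.

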**Table 4 pone.0355623.t004:** RE-AIM outcomes.

RE-AIM dimension	Data source	Outcome
Reach	EHR	Percent of PrEP eligible women identified
Effectiveness	EHR	Percent of eligible women receiving PrEP prescription
Adoption	EHR	Percent of eligible women offered PrEP
Implementation	EHR Key informant interviews	Acceptability and feasibility of intervention as reported by staff, clinicians, and patients
Maintenance	EHR	Reach and implementation over time(Timeline: Months 13–60)

RE-AIM: Reach, Effectiveness, Adoption, Implementation, and Maintenance; EHR: Electronic Health Record; PrEP: Pre-exposure Prophylaxis

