## Discussion

As a result of the intervention, and per our sample size calculation, we anticipate that Black women within selected PPIL health centers will be more likely to receive PrEP prescriptions following implementation, contributing to an anticipated increase in PrEP uptake of up to 15 percent. This magnitude of impact would be statistically significant and clinically meaningful, supporting scale-up through PPIL and other family planning centers. The present study design is powered to detect small increases during the study period and will support future exploratory analyses to examine trends over time. During post-intervention analysis, we anticipate identification of important barriers and facilitators as a continuum during the implementation process at the patient, clinician, health center, and system levels.

As the duration of the intervention period will differ by health center due to the SW-CRT design, implementation outcomes will be assessed at various stages at the different study health centers. This variance will be a strength in analysis in that a wider variety of implementation experiences will be available to us; however, the health centers with the shortest intervention periods may provide somewhat limited evidence for measures such as implementation and maintenance. Throughout the study, we will monitor and evaluate procedure adaptations and modification as well as implementation processes at each health center; this support will include facilitating provider training, providing technical and logistical assistance such as EHR support, and serving as a resource for PrEP navigators and clinical champions. Additionally, we will measure the acceptability and fidelity of the intervention package to document strengths and weaknesses while determining the progress on achieving the primary and secondary clinical outcomes through regular analysis of EHR data.

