### Trial status

The study is registered under NCT06335121. The SW-CRT will take place over the course of 27 months, with implementation strategies being rolled out at one site every 3 months. The research team will modify procedures as needed to ensure successful implementation at each health center throughout the duration of the trial.

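### The primary model's single constant intervention coefficient represents the average effect only if the effect does not change with time since rollout, and no planned sensitivity analysis checks this

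*Protocol article*

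**What the plan says.** The Quantitative data section names a generalized linear mixed-effects model "with a random intercept for each PPIL site and fixed effects for the intervention and for each time interval". The Sample size section powers the trial on the same structure, a "mixed effects effectiveness model with a random intercept for clinic and intervention and time as fixed effects", and claims detection of a rise from 1% to 5% uptake "with >90% power at a two-sided alpha of 0.05".

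The planned sensitivity analyses are multiple imputation and missing-indicator approaches, both for missing covariates. Change over time appears only as work for later: the Discussion says the design "will support future exploratory analyses to examine trends over time".

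Three statements bear on whether the effect must be constant:
- The Discussion says that the length of the intervention period differs by health center.
- It also says that study-team support continues throughout the study.
- Trial status says: "The research team will modify procedures as needed to ensure successful implementation at each health center throughout the duration of the trial".

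Study design sets three-month steps, one site per step, a three-month baseline, and a three-month transition counted in neither condition.

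**The concern.** A single intervention term with a fixed effect for each period treats the effect as fully present at rollout and unchanged afterwards. If that fails, the coefficient is not an ordinary average of the effects at each length of exposure. Sites already exposed also serve as comparators for sites crossing over later, so their long-exposure effects can enter with a negative sign.

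The stake is the main conclusion. If prescribing builds up over several quarters, a package that works could be reported as nearly ineffective. If it fades, the reported effect could exceed what sites obtained on average, in a trial whose Discussion looks ahead to scale-up. Nothing pre-specified would reveal either case except plots of rates.

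A lesser issue is that a site intercept alone assumes that site rates move in parallel over time, and there are only eight sites.

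**Working it through.** **Inputs.** From Sample size: 8 clinics, 30 women per clinic per step, ICC 0.25, 1% rising to 5%, two-sided alpha 0.05. From Study design: one site per three-month step, a baseline quarter and an excluded transition quarter. From Trial status: 27 months, which is nine quarters. Fig 1 is not shown, so four layouts were run: 27 months without a transition, with the transition at the step, or with it before the step; and 30 months with the transition at the step.

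**The plan's own figures.**
- Odds ratios: (0.05/0.95)/(0.01/0.99) = 5.21 and (0.15/0.85)/(0.01/0.99) = 17.47, as stated.
- Power uses the linear stepped-wedge model at mean p = 0.03 with the ICC taken as a share of total variance (an assumption, as the article gives no scale). Total variance is 0.03 × 0.97 = 0.0291, site variance is 0.25 × 0.0291 = 0.00728, and the cell-mean residual is 0.75 × 0.0291/30 = 0.00073.
- Without a transition, generalized least squares gives SE 0.0111, so power = Φ(0.04/0.0111 − 1.96) = 0.949. A simulated logistic mixed model gives 94.0%. The claim of more than 90% reproduces.

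**Weights.** Let δ(k) be the effect in the k-th quarter of exposure. The expected coefficient is Σ w(k)δ(k), where w is the intervention row of (X′V⁻¹X)⁻¹X′V⁻¹Z. X holds the period indicators and the intervention column, and Z holds the exposure-quarter indicators. At ICC 0.25:

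| Layout | w(1), w(2), … |
|---|---|
| 27 months, no transition | 0.60, 0.38, 0.21, 0.07, −0.02, −0.08, −0.09, −0.07 |
| 27 months, transition at step | 0.65, 0.39, 0.18, 0.03, −0.06, −0.10, −0.08 |
| 27 months, transition before step | 0.74, 0.45, 0.22, 0.04, −0.08, −0.14, −0.14, −0.09 |
| 30 months, transition at step | 0.67, 0.42, 0.21, 0.06, −0.05, −0.11, −0.12, −0.07 |

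Each row sums to 1 apart from rounding. At ICC 0.05 and 0.01 the weights still turn negative at the fifth quarter, or at the sixth in one case (no transition, ICC 0.01).

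**Constant effect.** Because the weights sum to 1, a constant effect is recovered. In the simulated logistic model the median estimate was 1.66 to 1.74, against a true log odds ratio of 1.65.

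**Assumed shapes** (the article gives none). Worked example, 27 months with the transition at the step and build-up to full effect by quarter 4:
- Expected coefficient: 0.25(0.649) + 0.50(0.385) + 0.75(0.179) + 0.029 − 0.064 − 0.100 − 0.078 = 0.28.
- True average: (0.25 + 0.50 + 0.75 + 4 × 1)/7 = 0.79.

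Across the four layouts at ICC 0.25:

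| Assumed shape | Expected coefficient, share of full effect | True average |
|---|---|---|
| Full by quarter 2 | 0.63 to 0.70 | 0.93 to 0.94 |
| Full by quarter 4 | 0.16 to 0.31 | 0.79 to 0.81 |
| None in quarter 1, then full | 0.26 to 0.41 | 0.86 to 0.88 |
| Linear waning to zero | 1.07 to 1.21 | 0.50 |

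For the four-quarter build-up the coefficient recovers 20% to 38% of the true average at ICC 0.25, and 41% to 51% at ICC 0.01.

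**Check on the logistic scale.** In the two 27-month layouts with a transition, power was about 88% under a constant effect. It fell to 12% to 16% under the four-quarter build-up, with median log odds ratios of 0.39 and 0.53.

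**Error rates** (simulated, Wald test at 1.96, Monte Carlo error about 1 to 2.5 points):
- Only a site intercept in the data: type I error 5.0% to 7.5%.
- Assumed site-by-period variance at 25% of site variance: 8% to 10% at a 1% baseline, and 13% to 15% at a 5% baseline.
- Assumed site-specific effect SD of 0.5 on the logit scale: 7% to 10% at a 1% baseline.

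**Price of the time-averaged effect** (separate indicator per exposure quarter, equal weights, ICC 0.25, difference 0.04):

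| Layout | SE, constant | SE, averaged | Ratio | Power |
|---|---|---|---|---|
| 27 months, no transition | 0.0111 | 0.0184 | 1.66 | 95% to 58% |
| 27 months, transition at step | 0.0133 | 0.0204 | 1.54 | 85% to 50% |
| 27 months, transition before step | 0.0133 | 0.0260 | 1.95 | 85% to 34% |

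**The case against.** **The plan does not predict a changing effect.** A reader might infer from the Maintenance row of Table 4, "Reach and implementation over time", and from the statement on modifying procedures that the plan expects a gradual effect. It does not say so. Maintenance concerns reach and implementation, and effectiveness is a separate row with no time pattern. Modifying procedures is not a forecast of growth. This stands: the shapes above are illustrations, and the documents support only that change is possible.

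**Early learning is partly handled.** The transition quarter is excluded from both conditions and is meant to make staff comfortable with the new systems. Rates will also be plotted by period and by center. Both help. But the transition precedes implementation, and every transition layout still has negative late weights. Plots change neither the estimate nor its p-value.

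**The error-rate evidence is conditional.** A reader might infer that type I error is inflated as planned. The documents do not support that. Without site-by-period or site-specific effect variation it is near nominal. The article also names no test or reference distribution, so the 1.96 cutoff is an assumption, and an unseen analysis plan may settle it.

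**The obvious remedy is expensive.** Making the time-averaged effect decisive would cost a large share of the power. The last exposure quarter rests on one site and 30 women, or 0.3 to 1.5 expected events at 1% to 5% uptake. This stands and shapes the fix.

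**Conclusion.** The point holds in conditional form. The weight pattern follows from the documented layout and model, and it does not depend on which transition layout applies or on the ICC values tried. The bias arises only if the effect varies with time since rollout. It is then substantial: about 16% to 31% of the full effect against a true average near 80% for a four-quarter build-up, and a little over twice the true average for linear waning (1.07/0.50 = 2.1 to 1.21/0.50 = 2.4). These figures assume ICC 0.25, 30 women per site-quarter and linear-scale weights, and the logistic simulation agrees for the build-up.

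It would go too far to call the primary model wrong or to say that the trial will understate its effect, because under an immediate, constant effect the model is unbiased. The defect is that the article fixes the model and lists sensitivity analyses that leave its most consequential assumption untested. The variance issue is secondary.

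**What to change.** Keep the constant-effect model as the primary analysis and add the following before outcome data are examined:

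1. A sentence stating that the coefficient is interpretable as the average intervention effect only if the effect does not vary with time since rollout.
2. A pre-specified sensitivity analysis reporting the exposure-time-averaged effect beside the primary estimate. A random or smoothed exposure-time effect is preferable to separate indicators, given how thin the last quarter is. State that the conclusion will be qualified if the two differ materially, and define materially in advance.
3. As secondary robustness checks, a site-by-period random effect, and either a permutation test over the 8! = 40,320 site orders or a small-sample t reference suited to eight sites.

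The cost is analysis wording and code, with no change to conduct. The time-averaged estimate will be imprecise: its standard error is about 1.5 to 2 times larger, with linear-scale power of about 34% to 58% instead of 85% to 95% in 27 months at ICC 0.25. A non-significant time-averaged result should therefore not be read as contradicting the primary test. The site-by-period variance may also be poorly estimated at 30 women per cell.
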